#### Data analysis

The statistical analysis will be conducted using SAS software (version 9.4). According to the “intention to treat” principle, the full analysis set (FAS) is defined as all participants randomized in the trial, with at least one experimental drug treatment history and at least one therapeutic session visit. Per protocol set (PPS), exclude participants found to be ineligible after randomization or deviate from the intervention or follow-up protocols. The safety analysis set will include all randomized patients who have completed at least one study visit. Finally, we will draw conclusions according to the analysis results of FAS. PPS will be used for sensitivity analysis.

For quantitative data meeting normal distribution, means with standard deviations will be calculated, otherwise, medians with quartile ranges will be shown. While for qualitative data, frequencies and percentages will be described. Comparison between groups will be performed by independent t-tests, or Wilcoxon rank-sum test for quantitative data, and the chi-square test or Fisher's exact test for qualitative data. Subgroup analyses will be conducted on those with PHQ-9 or GAD-7 scores ≥ 5 or < 5. Confounding factors that are difficult to control and unbalanced between groups will be used as covariates to analyze covariance to eliminate their influence on efficacy evaluation. *P* < 0.05 will be considered statistically significant. The last observation carried forward is supposed to estimate missing outcome data. Regarding safety, the number of AEs and SAEs will be categorized, and the incidence rate will be calculated. The data monitoring committee is not formally established because the trial has a short duration and known minimal risks. However, some form of data monitoring will undoubtedly be conducted by inspectors appointed by PI to ensure the accuracy and integrity of data.

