**Methods:**

This is a randomized, double-blind, placebo-controlled trial. 150 SCAD patients with qi deficiency, blood stasis, and liver qi stagnation syndrome are enrolled. Patients will be randomly allocated to the QTG or placebo groups at a 1:1 ratio. QTG and placebo will be added to the modern guideline-directed medical therapy for 12 weeks and patients will be followed up for another 24 weeks. The primary outcome is the improvement of metabolic equivalents measured by CPET. The secondary outcomes are cumulative incidence of composite endpoint events, other indicators in CPET, changes in the Seattle Angina Questionnaire, traditional Chinese medicine syndrome scale, 12 items of Short Form Health Survey Questionnaire, Patient Health Questionnaire-9, and Generalized Anxiety Disorder-7, changes of ST-T segment in the electrocardiogram, improvement of left ventricular ejection fraction and left ventricular end-diastolic diameter in echocardiography. In addition, metabolomics analysis will be performed based on blood samples. Adverse events and safety evaluations will also be documented. A full analysis set, per protocol set, and safety analysis set will be conducted.

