### Randomization, allocation concealment, and blinding

#### Random allocation

All patients who consent to participate and fulfill the inclusion criteria will be randomly assigned to the control or QTG group with a 1:1 allocation ratio. An independent statistician will generate the randomization sequence using center-stratified block randomization via SAS software (version 9.4). Treatment allocations will be put into opaque sealed envelopes sequentially numbered 1 to 150. A statistician will send the blind codes directly to the drug manufacturing room to label investigational products. Treatment allocation will not be disclosed until the primary endpoint is analyzed to ensure concealment. According to the clinical study program, the randomized code of drugs is the unique identification code of participants.

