1)Composite endpoint events include cardiovascular death, nonfatal myocardial infarction, revascularization, hospitalization for heart failure or unstable angina pectoris, stroke, and other thromboembolic complications. It will be recorded throughout the study. At the end of the 24-week follow-up period, the cumulative incidence of composite endpoint events will be compared between groups.2)Other indicators in CPET: (a) peak oxygen uptake (PeakVO_2_), percentage of predicted PeakVO_2_, oxygen pulse (VO_2_/Heart rate, VO_2_/HR), oxygen uptake related to work rate (ΔVO_2_/ΔWR), Ventilation Aerobic Threshold (VAT). These indicators reflect exercise capacity and cardiac function. (b) The partial pressure of end-tidal carbon dioxide (PETCO_2_), ventilatory equivalent for carbon dioxide slope (VE/VCO_2_ slope). These parameters measure the body's ability to exchange gases. Comparisons between groups will be made on the 12th week after enrollment.3)Seattle Angina Questionnaire (SAQ). SAQ is a valid self-administered scale that estimates five dimensions of health in patients with SCAD: physical limitation, anginal stability, anginal frequency, treatment satisfaction, and disease perception. SAQ will be measured at every visit. Changes from baseline in each dimension of SAQ will be compared between groups.4)TCM syndrome scale (TCMSS). The TCMSS is composed of related symptoms and signs (chest pain, chest tightness, palpitation, shortness of breath, spontaneous sweating, fatigue, distension in the hypochondrium, abdominal distension, heave a deep sigh, impatience and irritability, tongue manifestation, and pulse condition). Scores are assigned according to the severity of items. Measurement will be performed at each visit. The efficacy evaluation criteria are (a). Markedly effective: Clinical symptoms and signs are significantly improved, and syndrome scores are reduced by ≥ 70%. (b) Effective: Clinical symptoms and signs have improved; syndrome scores have been reduced by ≥ 30% and <70%. (c) Invalid: no significant improvement in clinical symptoms and signs, or even aggravation, syndrome score reduction < 30%. (d) Aggravation: The clinical symptoms and signs were aggravated, and the syndrome score decreased < 0.5)12 items of Short Form Health Survey Questionnaire (SF-12), Patient Health Questionnaire-9 (PHQ-9), and Generalized Anxiety Disorder-7 (GAD-7). SF-12, PHQ-9, and GAD-7 will be measured at each visit to evaluate patients' quality of life and current emotions of anxiety and depression, respectively. Changes from the baseline will be compared between groups.6)ST-T segment change in electrocardiogram, improvement of left ventricular ejection fraction (LVEF), as well as left ventricular end-diastolic diameter (LVEDD) in echocardiography will be compared between groups to assess the effect of QTG on myocardial blood supply and cardiac contractile functions at the 12th weeks after enrollment.7)Metabolomics analyses: Blood samples from ten participants per group will be elected randomly for metabolomic analyses. Liquid chromatography-mass spectrometry (LC-MS) and gas chromatography-mass spectrometry (GC–MS) will be adopted to detect the chemical and biological fingerprints, filter effective components, and explore the underlying metabolic pathways and target molecules of QTG for treating SCAD. Concerning the collection of blood samples, participants should fast for at least 8 h. 5 ml blood will be drawn into heparin sodium anticoagulant tubes, centrifuged, and plasma stored in Eppendorf tubes at −80°C.

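### The ordered TCM syndrome grades fall, on the natural reading, under a chi-square/Fisher rule that ignores order; an order-respecting test should be named and the overlapping grades separated

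*Protocol article*

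**What the plan says.** Item 4 of the secondary outcomes (section The primary and secondary outcomes) sets the efficacy criteria for the TCM syndrome scale as cut-points on the percentage fall in score:

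- Top grade: "Markedly effective: Clinical symptoms and signs are significantly improved, and syndrome scores are reduced by ≥ 70"%.
- Effective: "syndrome scores have been reduced by ≥ 30% and <70"%.
- Invalid: "no significant improvement in clinical symptoms and signs, or even aggravation, syndrome score reduction < 30"%.
- Aggravation: a worsening, with a score reduction below 0.

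The section Data analysis has one generic sentence on between-group tests. Quantitative data are compared by "independent t-tests, or Wilcoxon rank-sum test for quantitative data". Categorical data are compared by "the chi-square test or Fisher's exact test for qualitative data". P < 0.05 "will be considered statistically significant". No ordinal or trend test is named, and the sentence does not say which branch the syndrome grades take.

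The abstract also lists the scale among the change outcomes: "changes in the Seattle Angina Questionnaire, traditional Chinese medicine syndrome scale".

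**The concern.** The grades are ordered, and the clinical question is whether patients on the study granule sit higher on that order than patients on placebo. A Pearson chi-square or Fisher test on a two-row, four-column table has a different null: all four proportions are equal. Its p-value is the same if the columns are shuffled, so it cannot tell a move towards the top grade from a spread to both ends.

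Two things follow. First, a significant p-value does not by itself show benefit. Second, when the granule does move patients upward, a test that divides its sensitivity over three degrees of freedom finds it less often than a test aimed at the shift. The grades are what the article calls the efficacy criteria for this scale, so a reader is likely to take their p-value as the efficacy result.

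**Working it through.** **Inputs from the article.** Allocation: "randomly assigned to the control or QTG group with a 1:1 allocation ratio". Total 150, so 75 per arm. Dropout 20%, so 75 × 0.80 = 60 per arm evaluable. Significance level 0.05, taken as two-sided because the section Data analysis does not say.

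**The plan's own figure.** The only stated calculation is for METs, and it fixes the arm sizes. Net difference 1.38 − 0.42 = 0.96, standard deviation 1.56, one-sided 2.5%, power 90%. Then n per arm = 2 × (1.960 + 1.282)² × 1.56² / 0.96² ≈ 55.5, rounded up to 56, or 57 with the t distribution. 57 / 0.80 = 71.25, rounded up to 72, and 2 × 72 = 144. The stated 144 is reproduced, so 60 and 75 per arm are sound inputs. No power or response rate is given for the syndrome grades.

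**Assumed inputs.** Six control distributions over the four grades (for example 10/40/40/10%, 15/40/35/10% and 20/50/25/5%). Treated arms were obtained by a common odds ratio of 1 to 4. Each setting was simulated at least 20,000 times, comparing the Pearson chi-square with the tie-corrected Wilcoxon rank-sum test.

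**Step 1: no difference between arms.** Both tests reject about 5% of the time. Each is valid for its own null.

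**Step 2: a spread without net gain.** Control 10/40/40/10%, treated 20/30/30/20%. By symmetry, a random treated patient is as likely to be better as worse than a random control patient. The chi-square noncentrality is n × Σ(p − q)²/(p + q) = n × (2 × 0.01/0.30 + 2 × 0.01/0.70) = 0.0952n. That is 5.71 at n = 60 and 7.14 at n = 75. With three degrees of freedom this gives rejection in 50% and 60% of trials, and simulation agrees. Wilcoxon rejects in about 5%. A milder spread, treated 18/32/32/18%, gives about 34% and 42% against about 5%.

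**Step 3: a real upward shift.** With control 10/40/40/10%:

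| Odds ratio | n per arm | Chi-square power | Wilcoxon power |
|---|---|---|---|
| 2.0 | 60 | 36% | 53% |
| 2.0 | 75 | 45% | 62% |
| 2.5 | 60 | 59% | 76% |
| 2.5 | 75 | 70% | 85% |

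Over all six control distributions and both arm sizes, the loss in percentage points was:

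| Odds ratio | Four grades |
|---|---|
| 1.5 | about 8 to 10 |
| 2 to 2.5 | about 14 to 18 |
| 3 to 4 | about 2 to 14 |

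**Step 4: a check that needs no response rates.** At equal noncentrality, ordinal (one degree of freedom) power of 60/70/80/85/90% corresponds to 43/53/64/71/78% with three degrees of freedom, a loss of 17/17/16/14/12 points.

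**Step 5: are there four categories?** As written, invalid covers any reduction below 30% and expressly takes in worsening, so it contains aggravation (reduction below 0). A worsened patient fits both grades. If the two are merged, three levels and two degrees of freedom remain. The loss is then about 1 to 10 points over odds ratios of 1.5 to 4. The same asymptotic check gives 71% against 80%, about 9 points.

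**The case against.** The strongest reply is that the article never assigns a test to these grades. The section Data analysis is generic, an article condenses the full protocol, and the test for each secondary outcome is often left to a statistical analysis plan that is not shown. The score change named in the abstract is quantitative, so it can be tested by t-test or Wilcoxon, and a spread to both ends would generally show no shift there. Percentages per grade will also be tabulated, so a rise in aggravation would be visible.

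Much of this stands. The assignment is an inference, and the score analysis limits the harm. It does not remove the point: the article does state a rule for categorical data, that rule offers only tests that ignore order, and the same sentence ties Wilcoxon to quantitative data. Testing the score does not repair the test of the grades.

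Three stronger readings should be resisted:

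- A reader might infer that the chi-square test has an inflated type I error, since it rejects 50 to 60% of the time in Step 2. It does not. The distributions there truly differ, so rejecting equality is correct. The error would lie in reading the result as improvement. The scenario is constructed, and nothing in the article predicts such an effect.
- A reader might take a 14 to 18 point loss as a fixed property of the plan. It depends on response rates and an effect size that the article does not give.
- A reader might say that a spread would be reported as a benefit. The article does not say how such a result would be reported.

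**Conclusion.** The point holds in a limited form. On the natural reading, ordered grades go to a test that ignores order. Significance would then need the table of percentages before it could be called improvement, and moderate upward shifts would be missed more often than necessary. The size rests on assumed response rates, proportional odds, a two-sided 5% level and 60 to 75 per arm: about 2 to 18 points of power over odds ratios of 1.5 to 4, largest at 2 to 2.5, and clearly smaller if the two lowest grades become one. The overlap between those grades is a separate defect on the face of the text and has to be resolved before any four-level analysis. This concerns one derived grading of one secondary outcome; the METs analysis and sample size are untouched. It is worth correcting but does not threaten the trial.

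**What to change.** 1. In item 4 of the secondary outcomes, make the grades mutually exclusive, so that a patient whose score worsens falls in exactly one grade, or merge the two lowest grades and say so.
2. In Data analysis, add that ordered categorical outcomes, namely the syndrome grades, are compared by the tie-corrected Wilcoxon rank-sum test or by the row-mean-score Cochran-Mantel-Haenszel test stratified by centre, which matches the centre-stratified randomization. Report a proportional-odds ratio with its 95% confidence interval and tabulate the percentage in each grade by arm.
3. Keep chi-square and Fisher for binary or unordered outcomes.

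The cost is a short edit in two places and a standard analysis option, with no extra data or patients. The change should be made before the groups are unblinded, so that the test is not chosen after seeing results. The small downside is that an ordinal test is less sensitive to differences that are not a shift, which is why the percentages per grade should still be shown.

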#### Unblinding and emergency unblinding

This study has second-level blinding. After all the research data are checked and locked, the principal investigator (PI) and statistician will conduct the first unblinding, revealing the groups (such as groups A and B) to which each random number belongs. After completing the statistical analysis and clinical trial summary report, the second unblinding will be performed at the closing meeting to uncover the actual drug (QTG or placebo) each group takes.

Emergency unblinding is permissible only in exceptional circumstances, such as severe adverse events suspected to be related to the investigational products when knowledge of the actual treatment is essential for further patient management. Once unblinded, the participant will withdraw from the study. Researchers should report to the PI and ethics committee immediately and report the reasons for unblinding within 24 h. Investigators must record all code breaks with reasons as they occur on the corresponding case report form (CRF) pages.

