#### Sample size calculation

The sample size calculation is based on the superiority trial hypothesis test and is driven by the expected improvement in metabolic equivalents (METs). Referring to data from preliminary clinical trials (27, 28), we assume that the minimum difference in improvements of METs between groups over a 12-week treatment period would be 1.38, and the combined standard deviation would be 1.56. According to relevant literature and experts' advice, the superiority margin is 0.42. Considering a 20% dropout rate and referring to calculation results from PASS 15.0 software, 144 participants would achieve 90% power and a one-sided 2.5% significance level. For the convenience of randomization, a sample size of 150 is identified.

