#### The primary and secondary outcomes

The primary outcome is the improvement of METs in CPET. METs are an important indicator for evaluating aerobic metabolism and cardiorespiratory fitness. 1 MET equals 3.5 ml O_2_/kg/min. An increase in exercise capacity manifested by MET can bring great survival benefits. Small increases in cardiorespiratory fitness (e.g., 1–2 METs) are associated with considerably (10% to 30%) lower adverse cardiovascular event rates (30). CPET will be performed at baseline and the end of the 12-week treatment period. Changes from the baseline will be compared between groups.

The secondary outcomes are as follows:

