There also exist some limitations to this study. First, a 12-week therapeutic session and a 24-week follow-up visit are set. The relatively short duration of follow-up may be difficult to observe the occurrence of MACEs. However, previous studies have demonstrated that higher exercise tolerance is a good surrogate marker for long-term prognosis (13, 35, 36), so this trial may infer some guidance significance in Chinese herbal medicine improving the prognosis of SCAD. Second, the manufacturers of CPET equipment at four centers are not in full accordance with each other, so this may infer some measurement bias. While we will conduct unified training for outcome assessors concerning the operation scheme of CPET before trial initiation.

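### Covariates enter the analysis of METs only if found unbalanced: this gives up precision from baseline METs and leaves the adjusted model open, though the unadjusted test is valid and adequately powered

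*Protocol article*

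**What the plan says.** The primary outcome is improvement in METs: "CPET will be performed at baseline and the end of the 12-week treatment period. Changes from the baseline will be compared between groups" (The primary and secondary outcomes). The Data analysis section singles out no model for this outcome. Its one sentence on quantitative data reads: "Comparison between groups will be performed by independent t-tests, or Wilcoxon rank-sum test for quantitative data". Covariance analysis appears once, as a conditional step: "Confounding factors that are difficult to control and unbalanced between groups will be used as covariates to analyze covariance". The article names no covariate, gives no criterion for imbalance, and does not say when the decision is taken.

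Three other passages bear on the point.
- Random allocation: the sequence is blocked and stratified by centre. Four hospitals take part. Centre appears nowhere in the analysis.
- Discussion, limitations: "the manufacturers of CPET equipment at four centers are not in full accordance with each other".
- Unblinding and emergency unblinding: after database lock, the principal investigator and statistician "will conduct the first unblinding, revealing the groups (such as groups A and B) to which each random number belongs". The statistical analysis follows this step.

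**The concern.** In a randomized trial, baseline imbalance arises by chance. A covariate is worth adjusting for because it predicts the outcome, whether or not it happens to differ between arms. Baseline METs is the obvious predictor of week-12 METs and is already collected. Under the stated rule it enters the model only if it is judged unbalanced, so in most realisations of the trial its precision would go unused. Centre, which restricted the randomization, has no place in the analysis either.

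The second issue is that the model is not fixed. Without a criterion or a list, two analysts following the text could reach different covariate sets, and the decision can be taken once the coded groups are visible. It is then unclear whether the adjusted or the unadjusted difference is the primary result.

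This is not a detail left to an unseen analysis plan. The article states a rule, and an analysis plan that fixed baseline METs and centre in advance would have to depart from it.

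**Working it through.** **Inputs** (Sample size calculation). On the effect: "we assume that the minimum difference in improvements of METs between groups over a 12-week treatment period would be 1.38". On the spread: "the combined standard deviation would be 1.56". The superiority margin is 0.42, one-sided alpha 2.5%, power 90%, dropout 20%, stated N 144, enrolled N 150.

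**Reproducing the stated figure.** Net difference = 1.38 − 0.42 = 0.96. With SD 1.56 and an unadjusted two-sample t-test (noncentral t), 90% power needs 57 per arm. 57 / 0.8 = 71.25, rounded up to 72 per arm, or 144 in total. The figure reproduces, so the sample size rests on an unadjusted comparison of change.

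**Power of the unadjusted test at the planned size.** 150 × 0.8 = 120, or 60 per arm. Standard error = 1.56 × √(2/60) = 0.285. Noncentrality = 0.96 / 0.285 = 3.37. Power is 91.7%.

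**Effect of fixed adjustment for baseline.** Let the variance be σ² at both visits and the correlation r.
- Change score: variance 2σ²(1 − r).
- ANCOVA on baseline: residual variance σ²(1 − r²).
- Ratio: (1 − r²) / [2(1 − r)] = (1 + r)/2.
- Effective SD: 1.56 × √[(1 + r)/2].

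The article does not give r, so a range is shown.

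| r (assumed) | Variance ratio | Effective SD | SE at 60/arm | Power at 60/arm | Total N for 90% power, 20% dropout |
|---|---|---|---|---|---|
| unadjusted | 1 | 1.56 | 0.285 | 91.7% | 144 |
| 0.5 | 0.75 | 1.35 | 0.247 | 97.1% | 108 |
| 0.6 | 0.80 | 1.40 | 0.255 | 96.2% | 116 |
| 0.7 | 0.85 | 1.44 | 0.263 | 95.2% | 124 |
| 0.8 | 0.90 | 1.48 | 0.270 | 94.1% | 128 |
| 0.9 | 0.95 | 1.52 | 0.278 | 92.9% | 136 |

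Under equal variances the ratio is below 1 for every r below 1. The sponsor can find r from its preliminary data: since 1.56 = σ√[2(1 − r)], r = 0.5 corresponds to a single-visit SD of 1.56 and r = 0.9 to one of 3.49.

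**Type I error.** This was simulated with no true difference, 60 per arm, 20,000 runs at each of r = 0.5, 0.7 and 0.8, one-sided 2.5%, and baseline METs as the only candidate covariate.
- Unadjusted test: about 2.5%.
- ANCOVA always used: 2.3% to 2.4%.
- Mechanical rule (adjust if the baseline difference has p < 0.05): 2.2% to 2.3%.
- Free choice of the better of the adjusted and unadjusted results: 3.2% to 3.6%.
- In the roughly 5% of runs with significant baseline imbalance, the unadjusted change test rejected in about 9% to 17% (nominal two-sided 5%). Subtracting baseline does not fully remove a chance imbalance.

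**Centre.** The article has no between-centre variance of change, so the effect of a centre term cannot be computed.

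**The case against.** The strongest reply is that nothing here is invalid. Under randomization the unadjusted t-test on change is unbiased, the stated 144 reproduces under it, and power at the planned size exceeds the 90% target. Omitting the stratification factor makes the test conservative at worst. All of that stands.

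A reader might also infer several stronger claims, which the article does not support.
- **That baseline is ignored.** A change score uses baseline by subtraction, and baseline METs could enter under the imbalance rule. It is only not fixed in advance as a covariate.
- **That type I error is inflated.** A mechanically applied rule shows no inflation. Inflation appears only if the better result is picked freely, which the article does not say will happen; its wording directs that unbalanced factors be used. Analysts are described as blinded, and the A/B codes are not translated into QTG and placebo until the report is complete. This limits steering toward QTG, but it does not fix the covariate list. A blind review meeting precedes lock, but nothing says covariates are settled there.
- **That equipment differences bias the comparison and are met only by training.** Quality control also lists an operator consistency evaluation, a common ramp scheme, an unchanged work-rate increment per patient and consistent test times. Stratification tends to balance devices across arms, and a constant device offset cancels in the change score if the patient is retested on the same equipment.
- **That adding centre must raise power.** If centres differ little in mean change, the term only uses degrees of freedom.

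Finally, the t-test is a generic statement in a condensed article, not a labelled primary model. That is fair, but the imbalance rule is stated outright and is open to criticism as written.

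**Conclusion.** The point holds as a matter of efficiency and of fixing the model in advance. It does not show a biased or underpowered trial. The stated rule selects covariates on the wrong criterion, leaves that criterion undefined, and does not say which result is primary.

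The precision forgone from baseline METs is 5% to 25% of the variance. In power at 60 per arm this is about 1 to 5 percentage points above 91.7%. These sizes rest on equal variances at the two visits, an assumed r between 0.5 and 0.9, the planning SD of 1.56 for change, and 20% dropout. At the upper end of that range of r the gain is small. No size can be put on centre adjustment; the reason to include it is that the analysis should reflect the stratified randomization.

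The change should be made because it is nearly free and closes an avoidable choice, not because the planned test would fail.

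**What to change.** Name one primary analysis: ANCOVA of week-12 METs (or, equivalently for the treatment effect, of change) on treatment, baseline METs and centre, for all FAS patients whatever the observed balance. Test the adjusted difference against the 0.42 margin at one-sided 2.5%, as in the sample size section, and report it with its 95% confidence interval. Use the same form, own baseline plus centre, for the continuous secondary outcomes. Delete the imbalance-triggered rule, or confine it to a sensitivity analysis labelled as such. The unadjusted comparison can remain as a supportive result. Make the change before the A/B labels are revealed.

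The cost is wording and, for four centres, three degrees of freedom, plus one for baseline, out of about 118. All the variables are already collected, and no patients or visits are added. How missing week-12 values are handled is a separate question that this change does not touch.

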In traditional Chinese medicine (TCM), the core pathogenesis of SCAD is “deficiency in origin and excess in superficiality”, while anxiety and depression are associated with liver-qi stagnation. Qi deficiency can lead to blood stasis, and it can also result in qi stagnation. In other words, this is “excess resulting from deficiency”. Based on this theory, Qixue Tongzhi Granule (QTG) is transformed from Xuefu Zhuyu decoration by academician [name]. QTG consists of *Astragali radix*, *Chuanxiong rhizoma*, *Paeoniae radix rubra*, *Corydalis rhizoma*, and *Aurantii fructus*, having the function of tonifying qi, promoting blood circulation, and regulating qi-flowing. During the 8th, 9th, and 10th Five-year National Science and Technology Attack Plan, academician [name]'s team conducted a series of clinical trials to evaluate the effect of optimized formulas of Xuefu Zhuyu decoration, such as Xuefu Zhuyu condensed pills, refined Xuefu capsule, Xiongshao capsule, on preventing restenosis after coronary intervention (15, 16). Declined exercise capacity and fatigue are common clinical manifestations in CHD patients. Evidence from the basic research shows that *Astragali radix* can increase exercise capacity and resist fatigue in mice (17, 18). Moreover, *Astragali radix* can lower cholesterol levels and improve self-reported vigor in older adults (19). Active ingredients extracted from *Paeoniae radix alba*, *Corydalis rhizoma*, *Aurantii fructus*, and *Astragali radix* have antidepressant effects in animal models (20–23).

Under the direction of disease integration with the syndrome theory, we aim to investigate the efficacy and safety of QTG in improving exercise capacity, alleviating angina pectoris, anxiety/depression symptoms, promoting the health-related quality of life, and reducing the risk of composite endpoints in subjects with SCAD. Until now, Chinese and Western medicines verified to be effective in improving aerobic capacity and prognosis of CHD are rare. This study may present a novel, promising treatment option for CHD patients with low cardiorespiratory fitness and psychological imbalance.

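### The repeatedly measured scales have no named comparison visit, while any P < 0.05 is called significant, leaving 20 to 47 secondary comparisons open to a chance finding of benefit

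*Protocol article*

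**What the plan says.** The Data analysis section of the protocol article sets one threshold, P < 0.05, below which a result "will be considered statistically significant". Quantitative outcomes go to an independent t-test or Wilcoxon rank-sum test, and qualitative ones to a chi-square or Fisher's exact test. Covariates enter only for factors found to be unbalanced, and missing outcomes are filled by LOCF. The section ranks no secondary outcomes and does not call them exploratory.

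On SAQ, the outcomes section says: "Changes from baseline in each dimension of SAQ will be compared between groups". It adds that "SF-12, PHQ-9, and GAD-7 will be measured at each visit" and that their changes from baseline are compared too. The TCM syndrome scale (TCMSS) is also scored at each visit and has four response categories. No comparison visit is given for any of these.

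The same section does give a time elsewhere: week 12 for the other exercise-test indicators and for ECG and echocardiography, and the end of follow-up for the composite.

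The Introduction lists among the aims "alleviating angina pectoris, anxiety/depression symptoms, promoting the health-related quality of life, and reducing the risk of composite endpoints", alongside exercise capacity.

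**The concern.** Under the plan as written, a difference on any of these scales at any of four visits may be called significant. The visits are not interchangeable. Treatment lasts 12 weeks, so weeks 4 and 12 are on-treatment site visits, while weeks 24 and 36 are telephone contacts after treatment has stopped. An effect at week 4 and an effect at week 36 answer different questions, and the plan does not say which one decides.

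This matters because angina, mood and quality of life are stated aims, and the article presents the granule as an option for patients with psychological imbalance. Such a claim can rest only on these scales. If the visit can be chosen after the results are seen, a chance difference can be reported as efficacy.

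LOCF is a missing-data weakness in its own right, but it bears on this point. With 20% dropout assumed, an early chance difference among those who leave is copied into later visits and can look like a lasting effect.

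**Working it through.** **1. The plan's own figure, for reference.** The sample size section assumes that "the minimum difference in improvements of METs between groups over a 12-week treatment period would be 1.38", that "the combined standard deviation would be 1.56" and that "the superiority margin is 0.42".

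- Net difference: 1.38 − 0.42 = 0.96.
- Normal approximation: n per arm = 2 × (1.960 + 1.282)² × 1.56² / 0.96² = 55.5, so 56.
- With the t distribution, power is 0.898 at 56 per arm and 0.903 at 57, so 57 are needed.
- With 20% dropout: 57 / 0.80 = 71.25, so 72 per arm and 144 in total.

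This matches "144 participants would achieve 90% power and a one-sided 2.5% significance level". The calculation covers one test, on METs, with its error rate unsplit. The article states no count or error rate for the secondary outcomes.

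**2. Counting the secondary comparisons.** SF-12 is counted as one score.

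| Outcome | One visit per scale | All four visits |
|---|---|---|
| SAQ, five dimensions | 5 | 20 |
| SF-12 | 1 | 4 |
| PHQ-9 | 1 | 4 |
| GAD-7 | 1 | 4 |
| TCMSS | 1 | 4 |
| Other exercise-test indicators (week 12) | 7 | 7 |
| ST-T, LVEF, LVEDD (week 12) | 3 | 3 |
| Composite (end of follow-up) | 1 | 1 |
| **Total** | **20** | **47** |

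Two SF-12 summary scores would make the second total 51. The planned PHQ-9/GAD-7 subgroups are not counted.

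Angina, mood and quality of life (SAQ, SF-12, PHQ-9, GAD-7) account for 5 + 1 + 1 + 1 = 8 comparisons at one visit each, or 8 × 4 = 32 over four visits.

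**3. Chance of at least one false benefit.** Assume no true effect and a two-sided P < 0.05, so each test has a 2.5% chance of a significant result in favour of the granule. The article does not give the sidedness of its threshold.

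- Independent tests: 1 − 0.975^m. For m = 8 this is 18.3%; for m = 32 it is 55.5%.
- Common correlation ρ between test statistics: 1 − ∫ φ(u) Φ((1.96 − √ρ·u)/√(1 − ρ))^m du.

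| Tests m | ρ = 0 | ρ = 0.3 | ρ = 0.5 | ρ = 0.7 |
|---|---|---|---|---|
| 1 | 2.5% | 2.5% | 2.5% | 2.5% |
| 8 (one visit each) | 18.3% | 15.2% | 12.5% | 9.5% |
| 32 (four visits each) | 55.5% | 36.2% | 26.2% | 17.3% |

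The article gives no correlations, so these are assumed. A simulation that separated correlation between endpoints (0.3 to 0.7) from correlation between visits (0.5 to 0.7) gave about 21–39% for the 32 tests and 9–15% for the 8, inside or close to the ranges above.

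**The case against.** **Measured is not tested.** The article says that the scales are measured at each visit and that changes are compared. It does not say that they are compared at each visit. A reader might infer a commitment to at least 47 tests. The text does not support that: 47 is the count if every visit is tested, and the same sections give 20 at one visit per scale. This objection stands, so both counts are given.

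**The largest available percentage measures something else.** Over 47 independent tests, the chance of any P < 0.05 is 1 − 0.95^47 = 91.0%. A reader might take this as the chance of a false claim of benefit. It is not: it counts results favouring placebo, assumes independence, and includes exercise-test, ECG, echocardiography, TCMSS and composite comparisons. Only 32 of the 47 concern angina, mood or quality of life.

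**Confirmatory status is already visible.** There is one primary outcome, the sample size rests on it alone, and everything else is labelled secondary. This stands for the primary test. It does not settle the secondary claims, because the significance sentence makes no distinction.

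**An unseen analysis plan may set a hierarchy.** True, and the absence of one here would not by itself be a finding. But the article does fix comparison times for its other outcomes and leaves only the repeated scales open. It also commits to unadjusted two-sample tests with LOCF.

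**Separate visit tests are valid one at a time, and correlation between visits lowers the overall error rate.** Both statements are correct, and the table allows for the second. Neither answers which visit decides.

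**Conclusion.** The point holds in a limited form. One significance rule covers 20 to 47 secondary comparisons, and the scales that carry the claims on angina, mood and quality of life have no deciding visit. With no true effect, the chance of at least one false benefit in those domains is about 10–18% at one visit per scale and about 17–56% if all four visits are tested, against 2.5% for one test. The ranges rest on an assumed common correlation from 0.7 down to zero, on SF-12 as one score, and on a two-sided threshold.

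The type I error of the primary METs comparison is not changed by any of this. A reader might infer that the trial's main conclusion is unsafe or that a false secondary claim is near certain; the documents support neither. This is an inexpensive improvement that should be made before unblinding, not a flaw in the primary analysis.

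**What to change.** For each continuous repeated score (the five SAQ dimensions, SF-12, PHQ-9, GAD-7 and the TCMSS total), replace the visit-level two-sample tests with LOCF by one mixed model for repeated measures. Its terms are baseline score, centre, treatment, visit and treatment by visit; centre belongs there because randomisation is stratified by it. Name week 12, the end of treatment and the time of the primary outcome, as the deciding contrast. Report weeks 4, 24 and 36 as estimates with 95% confidence intervals.

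Compare the TCMSS response categories at week 12 only. The tested secondary comparisons then fall from as many as 47 to 20, or 21 if TCMSS is reported both as a total and in categories.

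Because eight endpoints at one visit still carry a 10–18% chance of a false benefit, also state that only METs is confirmatory and that secondary P values are nominal. Limit the P < 0.05 sentence accordingly.

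The cost is analysis wording and standard models in the SAS software already planned, on data already collected. The model needs no carried-forward values but assumes that missing visits are missing at random. The downside for the sponsor is that a secondary result can no longer be called significant at whichever visit happens to reach P < 0.05. If a separate analysis plan already contains these rules, only this wording needs to be aligned with it.
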